## Abstract

**Introduction:**

To minimize the risk of developing foot-ulcers, persons with diabetes are given the advice to daily inspect their feet and to apply skincare formulations. However, commercially available skincare products have rarely been developed and evaluated for diabetes foot care specifically. The primary aim of this randomized controlled trial (RCT) is to evaluate the effects in reducing foot xerosis in persons with diabetes without foot-ulcers using two skincare creams containing different humectants (interventions) against a cream base non-humectant (comparator). Secondary outcomes are to evaluate differences on skin barrier integrity, low-molecular weight biomarkers and skin microbiota, microcirculation including transcutaneous oxygen pressure, degree of neuropathy, and HbA1c between intervention-comparator creams.

**Methods:**

Two-armed double-blind RCT, registered in ClinicalTrials.gov Identifier: NCT06427889. With 80 % power, two-tailed significance of 2.5 % in each arm, 39 study persons is needed in each arm, total 78 persons, 98 including dropouts, to be able to prove a reduction of at least one category in the Xerosis Severity Scale with the intervention creams compared to the comparator. In one arm, each participant will treat one foot with one of the intervention creams (Oviderm® or Canoderm®), while the opposite foot will be treated with the comparator cream (Decubal®lipid cream), twice a day. If needed, participants are enrolled after a wash-out period of two weeks. The participants will undergo examinations at baseline, day 14 and day 28.

**Discussion:**

This RCT evaluate the potential effects of humectants in skin creams against foot xerosis in persons with diabetes.

## Introduction

1

Diabetes mellitus is expanding globally, accounting for 2–5 % of the population in Europe. According to the International Diabetes Federation the prevalence of diabetes in Swedish adults is 6.8 % [1]. The prevalence of diabetic foot ulcers (DFU) is in the range of 4–10 % among the persons having diabetes [2] and the lifelong risk to develop a foot ulcer is as high as 25 % [3]. Approximately 50 % of people with diabetes and a foot ulcer have peripheral artery disease (PAD) and the presence of PAD significantly increases the risk of adverse limb and cardiovascular events [4]. Peripheral neuropathy alone, or in combination with PAD [5], is a serious complication to diabetes and can cause both dry skin and calluses leading to increased skin cracks and risk for development of DFU. DFU is a devastating complication that rapidly can lead to deep foot infection, amputation, sepsis, and death [4]. More than 60 % of all non-traumatic lower extremity amputations are due to diabetes mellitus [6]. DFU management is very resource demanding with great impact on costs for health care systems. In the event of amputation, the costs for rehabilitation are significant [7]. Life expectancy is reduced for persons with DFU [8,9].

In addition, patients with DFU report pain, mobility limitation, discomfort feelings and impairment of quality of life [10,11]. Hence, it of outmost importance to prevent the development of DFU [12]. To minimize the risk to develop ulcers, patients with diabetes are given the recommendation from health care professionals to daily inspect their feet and to use emollient [4]. In brief, an emollient is normally referred to a skincare product that softens and hydrates the skin by forming a protective barrier to reduce transdermal water loss. A moisturizer, on the other hand, is a formulation designed to hydrate the skin, usually by incorporating small polar substances referred to as humectants, which have water attracting properties. Thus, both emollients and moisturizers aim at promoting skin hydration but their mode of action differs. However, commercially available skincare products for treating dry skin in individuals with diabetes are seldom designed specifically for this demographic's skincare needs. Nevertheless, Garrigue et al. [13] showed that application of Pedimed® cream (contains humectants, i.e., 10 % glycerine, 5 % urea and 1 % lactic acid) twice a day, significantly reduced foot xerosis over its vehicle after 2 and 4 weeks of treatment in patients with diabetes [13]. In another study [14], the efficacy of improving skin dryness of the dorsal and plantar regions of feet of patients with type 2 diabetes was investigated by comparing Ureadin® (containing 5 % urea) with Dexeryl® (containing 15 % glycerol). Following visual inspection, it was concluded that application of Ureadin® resulted in significantly greater skin hydration compared to Dexeryl® with an 89 % reduction in dry skin area severity index score in comparison with baseline values [14].

Despite a few studies showing reduction of xerosis of diabetic skin by application of skincare products, there are no firm recommendations of skincare routines for persons with diabetes, specifying which type of creams they should use to reduce the risk of ulcers.

Therefore, the primary objective of this study is to evaluate the reducing effect of skin xerosis using two pharmaceutical skin care creams (cream A and cream B) containing different humectants, compared to a cream without any humectant (cream C).

## Materials and methods

2

*Overall-Design*: Two-armed double-blind randomized controlled clinical trial (RCT).

### Objectives of the study

2.1

The primary objective of this RCT is to evaluate the effect of two, humectant-containing pharmaceutical skin creams in reducing skin xerosis on feet of persons with diabetes without foot ulcers. The results will be compared to skin treatment with a humectant-free cream.

### Participants, setting, recruitment and randomization

2.2

Persons above 18 years with diagnosed diabetes having dry feet without foot ulcers will be contacted by the researchers and study nurses through diabetes societies and social media for the opportunity to be included in the study. This interventional study will be conducted within the facilities of Malmö University, Sweden.

#### Inclusion criteria

2.2.1

•Persons above 18 years of age diagnosed with any type of diabetes mellitus, with self-experienced dry skin.•Dry skin on both feet with a Xerosis Severity Scale (XSS) [15] score between two to six. No more than one XSS score in difference between the subjects' feet.•Ability to understand sufficient Swedish language to complete the necessary forms and understand the procedure of the study.

#### Exclusion criteria

2.2.2

•Known sensibility to any of the ingredients in the products.•Other diagnosed skin disease on the feet.•Active lesions on either foot.•Treatment with local medications, including topical moisturizers or keratolytic agents on the feet, within two weeks before the beginning of the study.•Potential study subjects judged unable to comply with treatment schedule and study specific information.•Female of childbearing potential that do not use effective medically accepted contraception.

#### Enrollment and randomization

2.2.3

Persons with diabetes will be introduced about the study at society meetings and at social media. Potential study participants that are suitable (according to the study criteria) for the study will be contacted and informed in more details about the study by the research nurses. Furthermore, a welcome letter will be sent by post to the participants with practical information. If acceptance and pass of criteria, informed consent form will be signed and the potential participants will be recorded in the research software program Research Electronic Data Capture® (REDCap) version 13.1.37. The participants will then be randomized and will adhere to the clinical study schedule and specific study procedures. The enrolled study participants will be given an autonomic code (in REDCap) as soon as the participants have signed the consent form. According to the code the participants will be randomized into different treatment, unknown which, for both the participants and the investigators (double-blind). Apart from the treatment randomization the participants will be randomized to which foot that will be treated with which cream. One foot will be treated with one interventional cream (cream A or B) and the contralateral foot with the comparator humectant-free cream (C).

#### Sample size estimation

2.2.4

This is a superiority RCT, where either of the intervention creams is hypothesized to be superior to the comparator cream in reducing XSS score during a four-week application period. To be able to prove this hypothesis, a total of 98 participants, 39 persons with diabetes in each arm for analysis, is needed, which is based on the following: A change in XSS score ≤1 is not regarded clinically important. The estimated intra-individual standard deviation for the difference in XSS score is 2.0. With 80 % power, two-tailed significance of 2.5 % in every arm, 39 evaluable study persons is needed in every arm, a total of 78 persons. If 20 % of persons are estimated not to be fully evaluable, sample size increases to 98 (78/0.8).

The following formula will be used to calculate the number of patients needed in each part of the trial [15,16] (N = number of fully evaluable patients in each part of the trial):$$N=\frac{\sigma_{d}^{2}\times {\left(\lambda_{\alpha }+\lambda_{\beta }\right)}^{2}}{\Delta^{2}}$$In the formula above σ_d_ is the standard deviation for the difference between the change in each treatment, Δ is the difference to detect between the treatments (a difference of at least 1 is assumed to be clinically relevant), λ_x_ is the x:th percentile of the standardized normal distribution. As the test is two-sided and the significance level should be 0.0250 (in order to keep the family-wise type I error at 5 % and there are two comparisons: Canoderm® versus Decubal® and Oviderm® versus Decubal) then λ_α_ = 2.1414. If the power is 80 % then λ_β_ = 0.8416 and if the power is 90 % then λ_β_ = 1.2816.

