### Statistical analysis

2.5

The primary analysis principle applied will be the intention-to-treat. All statistical analysis and data management will be performed using SPSS for Windows, version 28.0 (IBM, Armonk, NY, USA). Measurements, such as XSS score, TEWL, pH, impedance, abundance of the biomarkers will be used as continuous variables and treatment with the creams, gender, and patients grouping parameters will be used as categorical variables. Descriptive statistics such as number of participants, mean, median, standard deviation, minimum and maximum values will be summarized and tabulated. XSS score will be independently evaluated by a random sample of twenty photographs by a second dermatologist, for validation purposes, to be able to assess inter-rater reliability by calculating intraclass correlation with 95 % confidence intervals. The primary outcome of the study is to compare the change in XSS score from baseline until the end (4 weeks) due to treatment with moisturizing creams vs a comparator product. Prior to analysis of the XSS differences between the treatment groups, the distribution of the data will be tested for normality by performing Shapiro-Wilk and Kolmogorov-Smirnov tests, as well as inspecting quantile-quantile (QQ) plots. Homogeneity of variances will be tested by performing Levene's test. Comparison between two related groups, *e.g.*, application of the formulation on the left and right foot, will be done by paired two-sample *t*-test, whereas for unrelated two groups two-sample *t*-test will be performed. When neither homogeneity of variances nor assumption of normality will be fulfilled, a non-parametric Wilcoxon rank sum test will be applied. In case of comparison between more than two groups, *e.g.*, the effect of three creams, one-way ANOVA with multiple comparisons (Tukey's test) will be used. Alternatively, if assumptions of normality or homogeneity of variances will not be fulfilled, non-parametric Kruskal Wallis test will be performed. The effect of covariables, *e.g.*, age, on main effect, *e.g.*, XSS change upon the treatment with the cream, will be tested by performing ANCOVA analysis. To seek for the measurements capable to explain and predict the effectiveness of the diabetic foot treatment with different creams more complex statistical analysis will be performed. Principal component analysis (PCA), multiway ANOVA and mixed models, and multiple regression analysis and model selection will be performed on the data collected. Level of statistical significance was set to p<0.05.

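### Section 2.2.4 classes the powered XSS difference of 1 as both unimportant and relevant, and the abstract says the sample can prove a one-category reduction when the design tests only against zero

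*Protocol article*

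**What the plan says.** Section 2.2.4 (Sample size estimation) of the protocol article lists the grounds for 39 evaluable persons per arm. The first is "A change in XSS score ≤1 is not regarded clinically important"; the next is "The estimated intra-individual standard deviation for the difference in XSS score is 2.0". The following paragraph gives the paired sample-size formula, defines Δ as the between-treatment difference to be detected, and adds in brackets that "a difference of at least 1 is assumed to be clinically relevant".

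The hypothesis in the same section is ordinary superiority: "either of the intervention creams is hypothesized to be superior to the comparator cream in reducing XSS score". On the error rate it says: "As the test is two-sided and the significance level should be 0.0250".

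The abstract (Methods) states the purpose of the same 39 per arm differently: "to be able to prove a reduction of at least one category in the Xerosis Severity Scale with the intervention creams compared to the comparator".

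Section 2.5 (Statistical analysis) compares change in XSS from baseline to four weeks. It treats XSS as continuous and says that comparison of related groups, such as "application of the formulation on the left and right foot, will be done by paired two-sample" *t*-test, with a rank-based alternative. No margin or non-zero null value appears in any of these places.

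**The concern.** Two things do not fit.

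First, the trial is sized for Δ = 1. One statement in section 2.2.4 places 1 among the values that do not matter; the other places it among those that do. Taken literally, the first says that the trial is powered for an effect of no clinical importance.

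Second, the abstract names a conclusion that the test cannot deliver. Rejecting a null of zero shows that the mean difference is above zero. It does not show that the difference is one category or more.

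What is at stake is interpretation. If the estimate falls near 1, the article supports calling it relevant or not relevant, and the choice could be made after the result is known. A significant estimate below 1 could also be reported, in the abstract's terms, as proof of a one-category reduction.

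**Working it through.** **Inputs (section 2.2.4):** σ_d = 2.0; Δ = 1; two-sided alpha 0.025 per comparison; power 80 % (λ_β = 0.8416); 39 evaluable per arm; 20 % not fully evaluable.

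**1. Reproduce the plan's figures.** The formula is N = σ_d² × (λ_α + λ_β)² / Δ². The normal quantile for two-sided 0.025 is 2.2414.

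- N = 4 × (2.2414 + 0.8416)² / 1 = 38.02, rounded up to 39.
- Two arms: 78. With 20 % loss: 78 / 0.8 = 97.5, rounded up to 98.

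The stated figures reproduce. (The printed λ_α is 2.1414, which would give 35.59, so 36 per arm. The stated 39 therefore rests on 2.2414, and the printed value looks like a misprint. That is a separate matter.)

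**2. Identify the null value.** The article does not write it out. The hypothesis is superiority without a margin, the formula has no margin term, and the paired *t*-test is given no non-zero reference value. All three imply a null of 0.

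**3. Set the two relevance statements beside the input.**

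| Mean difference | First statement (≤1 not important) | Second statement (≥1 relevant) |
|---|---|---|
| Below 1 | not important | not covered |
| Exactly 1 (the Δ used) | not important | relevant |
| Above 1 | not covered | relevant |

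For a mean difference they collide at one point, which is the point used for sizing.

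**4. What 39 pairs deliver against zero.**

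- Standard error = 2 / √39 = 0.320.
- Smallest significant observed difference: 2.2414 × 0.320 = 0.72 (normal), or 2.334 × 0.320 = 0.75 (*t*, 38 degrees of freedom).
- Power at a true difference of 1: 81.1 % (normal) or 78.1 % (noncentral *t*).
- Chance of a significant result with an estimate below 1, if the true difference is 1 (normal): 0.811 − 0.500 = 0.311, about 31 %.

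**5. What a literal proof of more than 1 would take.** Here the null is a difference of 1 or less, and the lower 97.5 % confidence limit must exceed 1. The article gives no true difference other than 1, so 1.5 and 2.0 are assumptions that show the range.

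| Assumed true difference | Chance of success with 39 per arm | N per arm for 80 % power (normal) |
|---|---|---|
| 1.0 | 1.25 % | not attainable |
| 1.5 | 23 % (*t*) to 25 % (normal) | 38.02 / 0.5² = 152.1, so 153 |
| 2.0 | 78 % (*t*) to 81 % (normal) | 38.02 / 1² = 38.02, so 39 |

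**The case against.** The best defence is that the mismatch concerns a single boundary value. Both statements draw the line at 1 and differ only on whether 1 itself counts. The primary analysis compares means of a score treated as continuous, so an estimate of exactly 1 has little practical bearing. The article states no responder rule, where whole-number category changes would make the boundary matter. This stands, and it limits the weight of the point.

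It can also be said that the first statement speaks of a change, perhaps within a foot, and the second of a difference between treatments. This does not rescue the text. The first statement is offered as a ground for N, and the only effect-size input to N is the between-treatment Δ. No within-foot threshold enters the calculation. If two thresholds were meant, the article does not say so.

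On the abstract, the sentence may be a compressed power statement using the verb loosely. Section 2.2.4 is better worded: what is to be proved there is superiority, and Δ is a difference to detect. That softens the point, but the abstract still states a property that the design lacks.

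Finally, the figures in steps 4 and 5 are partly generic. Any trial with 80 % power reaches significance below its target difference. The 1.25 % is half of alpha by construction and would be the same in a faultless trial at this alpha. These figures show how far the literal reading of the abstract is from the design; they do not measure harm from the boundary mismatch.

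**Conclusion.** The point holds as a defect of wording and interpretation. Section 2.2.4 classifies its own powered difference in opposite ways, and the abstract promises proof of at least one category from a design that has about 80 % power only to reject zero when the true difference is 1. Significance is reached at an observed difference of about 0.75. These figures rest on the stated SD of 2.0, 39 evaluable pairs per arm, two-sided alpha 0.025 and a null of zero inferred as in step 2.

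A reader might infer three stronger things that the documents do not support:

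- **That the sample size is wrong.** It is not: 39, 78 and 98 follow from Δ = 1 tested against zero.
- **That the trial is knowingly powered for an irrelevant effect.** The second statement says the opposite, and the article does not settle which one governs.
- **That the trial has only a 1.25 % chance of success.** That would apply only if a lower confidence limit above 1 were the success criterion, and the article sets no such criterion.

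**What to change.** **Section 2.2.4:** the sponsor should reconcile the two statements into one pre-specified relevance threshold. It should say whether the threshold applies to within-foot change or to the between-foot difference in change, and whether 1 itself counts. The choice is the sponsor's; the article gives no basis for preferring one statement over the other. If a change of 1 or less is truly regarded as unimportant for the between-foot difference, the choice of Δ = 1 must be justified anew.

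**Abstract, Methods:** replace the claim to prove a reduction of at least one category with one of 80 % power to detect a mean between-foot difference of 1 category. In reporting, a significant result should not be presented as proof of a reduction of at least one category.

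A rule that the confidence limit must exceed 1 should not be added as a success criterion. It would change what the trial has to show and, by step 5, would need a true difference near 2.0 for about 80 % power with 39 per arm.

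**Cost:** text changes only, with N unchanged, if Δ = 1 stands. If it does not, the sample size has to be reconsidered.

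### The fixed 0.025 level for each primary comparison is valid but needlessly conservative: Holm's procedure keeps the same 5 % family-wise error, never rejects less, and gains power when both creams work

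*Protocol article*

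**What the plan says.** Section 2.2.4 (Sample size estimation) sets the multiplicity rule together with the sample size. The level is given as "As the test is two-sided and the significance level should be 0.0250", and the reason is given beside it: "in order to keep the family-wise type I error at 5 % and there are two comparisons". The two comparisons are each intervention cream against Decubal. The resulting requirement reads "With 80 % power, two-tailed significance of 2.5 % in every arm, 39 evaluable study persons is needed in every arm", and the Abstract repeats that "39 study persons is needed in each arm".

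The planning values are in the same section: "a difference of at least 1 is assumed to be clinically relevant", and "The estimated intra-individual standard deviation for the difference in XSS score is 2.0". The hypothesis is worded as "either of the intervention creams is hypothesized to be superior to the comparator cream".

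Section 2.5 (Statistical analysis) names a paired t-test for left-right comparisons within a person. It gives one general significance level of p<0.05 and does not repeat the 0.025. Neither section describes passing the level on from one comparison to the other.

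**The concern.** An equal split of 5 % over two tests is the Bonferroni rule. As stated, a cream with p = 0.03 remains unproven even when the other cream has already succeeded at 0.025. Withholding that second claim gains nothing in error control. Once the first hypothesis has been rejected, at most one true null hypothesis can remain if that rejection was correct, and it can be tested at the full 5 %. Holm's procedure uses this and holds the family-wise error at 5 % under any dependence between the tests.

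The loss falls on the second cream. Section 2.1 sets out to evaluate two humectant creams, and the Discussion hopes for recommendations on specific products, so a verdict on each cream matters and not only on the better one.

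**Working it through.** **Inputs.** From 2.2.4: difference Δ = 1, SD of the within-person difference 2.0, two-sided 0.025 per comparison, 80 % power, 39 evaluable persons per arm, 20 % not evaluable. From 2.5: paired t-test. From 2.2.3: each participant receives only one of the two intervention creams. The arms therefore contain different people, and the two tests can be treated as independent.

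**1. The plan's own figure.** The standard normal value for two-sided 0.025 is 2.2414.
- N = 2.0² × (2.2414 + 0.8416)² / 1² = 38.02, rounded up to 39.
- 2 × 39 = 78, and 78 / 0.8 = 97.5, rounded up to 98.

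Both stated figures are reproduced. The critical value printed in 2.2.4 ("then λ_α_ = 2.1414") would give 35.6, so 36. The 39 therefore rests on 2.2414. That misprint is a separate matter and changes nothing below.

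**2. Power of one paired t-test.** With n = 39 and 38 degrees of freedom, the noncentrality is (1/2.0) × √39 = 3.12.
- a = power at two-sided 0.025 = 0.7814
- b = power at two-sided 0.05 = 0.8605
- b − a = 0.0791

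The t-test gives slightly less than the 80 % from the normal formula.

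**3. Both creams have the planned effect.**

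| Probability | Fixed split | Holm |
|---|---|---|
| A given cream proven | a = 78.1 % | a + (b − a) × a = 0.7814 + 0.0791 × 0.7814 = 84.3 % |
| Both proven | a² = 61.1 % | b² − (b − a)² = 0.7405 − 0.0063 = 73.4 % |
| At least one proven | 1 − (1 − a)² = 95.2 % | the same, 95.2 % |

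The Holm formula for both creams follows from the rule: both p-values must be below 0.05, and they must not both lie between 0.025 and 0.05. Simulation agrees with these figures. With the normal approximation at n = 39, the chance of proving both rises from 65.8 % to 76.6 %. At exactly 80 % power per arm it rises from 64.0 % to 75.1 %. The size of the gain hardly depends on the approximation.

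**4. One cream has no effect.** Holm's power for the effective cream is 0.7814 + 0.0791 × 0.025 = 78.3 %, practically the same as under the split.

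**5. Family-wise error under Holm.**
- Both nulls true: 1 − 0.975² = 4.94 %, identical to the split.
- One null true and the other cream at the planned effect: 0.025 + 0.025 × 0.7814 = 4.45 %.

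It is at most 5 % in every case.

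**6. The gain expressed in participants.** To reach Holm's 73.4 % for both creams, the fixed split would need 47 evaluable persons per arm instead of 39. Enrolment would be 94 / 0.8 = 117.5, so 118 instead of 98.

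**The case against.** **The split is valid.** This is correct. A reader might infer that the plan fails to control its error rate or that 0.025 is wrong. The documents do not support that: the stated rule delivers the 5 % it promises. The point is only that a better rule is available at almost no cost.

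**The 0.025 stands in the sample-size section, and sizing at 0.025 is compatible with Holm at the analysis.** This stands in part. Holm's first step is 0.025, and an analysis plan that is not shown could add the second step. But 2.2.4 ties 0.025 expressly to family-wise control of the two comparisons, and the article gives no other multiplicity rule.

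**Section 2.5 says p<0.05, so the comparison may be with the wrong baseline.** If both tests were run at 0.05, power for both creams would be 0.8605² = 74.1 %, and Holm would not raise it. The family-wise error would then be 1 − 0.95² = 9.75 %, against the stated aim of 2.2.4. The mismatch between the two sections is a separate issue. The gain given here is measured against the rule in 2.2.4.

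**The plan may not aim to prove both creams.** The wording "either of the intervention creams is hypothesized to be superior to the comparator cream" can mean at least one, and the 80 % power is stated per arm. A reader might take the rise from 61 % to 73 % as a gain on the trial's declared goal. The documents do not settle that. If the goal is at least one cream, nothing is gained.

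**Holm is not entirely free of cost.** This stands. If 97.5 % intervals were reported, a second cream with p between 0.025 and 0.05 would be declared proven while its interval includes zero. A reader might assume that such intervals are already planned. They are not: the only intervals mentioned are 95 % intervals for inter-rater agreement.

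**Conclusion.** The point holds as a recommendation for efficiency. The fixed 0.025 per comparison is valid but discards power that Holm's procedure recovers at the same 5 % family-wise level.

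The gain is about 6 percentage points per cream (78 % to 84 %) and about 12 for both creams (61 % to 73 %). It rests on the plan's difference of 1 and SD of 2.0, on 39 pairs per arm, on independent arms, and on both creams having the full planned effect. The 84 % should not be read as an unconditional power: it falls back to about 78 % if the other cream does nothing. The 95 % chance of proving at least one cream does not change.

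**What to change.** Keep the sample size based on 0.025. Then, before unblinding:

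- State in 2.2.4, and add to 2.5, that the two primary comparisons are tested by Holm's procedure at a family-wise two-sided 5 % level: the smaller p-value against 0.025 and, only if that is significant, the larger against 0.05.
- Say in 2.5 that the general p<0.05 does not apply to these two comparisons separately.
- If power is restated, give about 84 % per cream and 73 % for both, with the condition that both creams have the planned effect.
- Name the confidence-interval convention for the primary comparisons, and note that simple 97.5 % intervals will not always agree with a Holm rejection of the second comparison.

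The cost is a few sentences in the protocol and, if one exists, the statistical analysis plan. No participants, visits or data are affected.
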